## Abstract

**Introduction:** School-based programmes may promote knowledge and skills required to address climate change and better health and well-being in adolescents, yet evidence of their effectiveness is limited. In preparation for evaluating the Public Climate School, a school-based intervention to promote climate awareness and action in adolescents, we conduct a pilot study intended to assess procedures for participant recruitment, retention, and data collection, data quality issues and to provide preliminary parameter estimates to guide sample size calculations. **Methods and analysis:** This unblinded, cluster-controlled pilot study targets students in twelve classes from grades seven to thirteen in German public schools. Seven and five classes were allocated to the intervention and waitlist control arms, respectively. The intervention consisted of (1) live lessons on YouTube, (2) climate-related challenges of the day, (3) workshops and (4) peer exchange sessions. Waitlist control classes participated three weeks later. Measures included the proportion of students completing baseline and follow-up surveys, a comparison of baseline characteristics between students in the retained subsample and those lost to follow-up, proportions of students completing online and paper–pencil-based surveys and problems during data collection based on information reported by teachers. Data quality was assessed as proportions of missing data, associations between missingness and sociodemographic measures using logistic regression models and basic psychometric properties of scales including ceiling effects and internal consistency. Intentions to reduce one’s ecological footprint, the primary outcome, and all secondary outcomes for effect estimation were assessed one week pre- and post-intervention from November to December 2021 using items adapted from internationally used instruments and will be investigated using generalised linear mixed models and intention-to-treat analyses. **Conclusions:** The pilot study will lay the methodological groundwork for a large-scale cluster-randomised effectiveness and process evaluation of the Public Climate School. If proven effective and rolled out more broadly, the Public Climate School has the potential to contribute meaningfully to national climate mitigation and adaptation efforts by reaching a substantial share of adolescents in public schools, including those traditionally less involved in climate action.

## 1. Introduction

Anthropogenic climate change is the biggest threat to health in the 21st century and has the potential to disrupt planetary systems as we know them [1,2,3,4,5,6,7]. Adolescents are particularly vulnerable to the negative effects of the accelerating climate crisis [8,9], particularly in terms of negative mental health effects [10,11,12]. Anxiety concerning the consequences of climate change is widespread among adolescents and impacts their daily functioning [13]. Moreover, a recent review highlighted that climate change places adolescents at risk of further adverse mental health outcomes, including post-traumatic stress disorder, depression, sleep disorders and substance abuse [10].

Adolescents can, however, play an important role as drivers of change. Together with other civil society stakeholders, they have propelled the Fridays for Future movement, demanding ambitious action to tackle the climate crisis at national and international levels [14], and contribute to numerous sustainability initiatives locally [15]. Additionally, preliminary evidence suggests a positive association between sustainability-related activities and individual well-being, pointing to the potential of adolescents’ climate action for the prevention of climate-associated mental health problems [16]. These observations provide support for ongoing efforts to promote climate mitigation and adaptation activities among adolescents.

To safeguard acceptable living conditions for future generations, approaches are needed that actively engage a broad spectrum of citizens in climate change mitigation and adaptation. In this context, large-scale school-based programmes may be useful as school attendance is mandatory in most countries, and programmes promoting climate awareness and action in schools could thus reach a substantial proportion of young people. School-based programmes have the potential to increase knowledge about the climate crisis, empower students to become change agents and thus provide a basis for them to initiate and contribute to meaningful climate action [17,18]. Recent evidence also suggests that both students and teachers desire substantially more opportunities for education on sustainable development (ESD) [19]. However, despite its greater implementation within school curricula, current efforts have fallen short in Germany and elsewhere [20,21].

Despite the potential of school-based programmes, empirical evidence on their effectiveness remains limited. Results of observational studies remain largely inconsistent, with some showing positive associations between ESD and students’ sustainability knowledge [22,23], attitudes [22,24] and behaviours [25] and others showing no relationship for the same outcomes [25]. To our knowledge, studies that test the effects of school-based ESD interventions on climate awareness and action, explore mechanisms linking these interventions to intended outcomes and assess contextual factors that potentially moderate intervention effectiveness, do not exist [19].

Recently, the Public Climate School (PCS), a multi-component school-based programme aiming to promote climate awareness and action among school students, has been developed and offered in collaboration with public schools in Germany to approximately 30,000 students each year since 2019 by Students for Future, an offshoot of the Fridays for Future movement. The content and delivery of the PCS is guided by the concept of ESD [26] and focuses on, inter alia, participatory teaching and learning methods, critical thinking and imagining future scenarios [27]. The PCS is a complex intervention comprising several interacting components, such as live online lessons, interactive workshops and peer exchange sessions, and engages different stakeholder groups including students, teachers, school principals and the team implementing the PCS. Anticipated effects, potentially influenced by a variety of contextual factors, include increased individual and collective efficacy beliefs, increased identification with civil society groups involved in climate action and pro-environmental behavioural intentions of students. To date, however, an evaluation of this programme has not been undertaken.

In the proposed EvalPCS Pilot Study, Students for Future partner with academics spanning diverse disciplines, including psychology, epidemiology, education research and sociology, to address feasibility concerns related to participant recruitment and retention, data collection, data quality and the required sample size for a future cluster-randomised effectiveness study. The pilot study thereby aims to lay the groundwork for a future comprehensive evaluation of PCS programme effectiveness, mechanisms of action and contextual factors affecting its implementation and effectiveness.

### Objectives

In this article, we describe the design of the EvalPCS Pilot Study. As primary objectives, we investigate:(1)Participant recruitment and retention;(2)Data collection;(3)Data quality.

As a secondary objective, we will obtain preliminary parameter estimates contributing to future sample size calculations. 

## 2. Methods and Analysis

### 2.1. Study Design

The study design reflects the updated UK Medical Research Council guidance on the development and evaluation of complex interventions and focuses on investigating the feasibility of the evaluation design, one of four phases in complex intervention research [28]. The pilot study is based on a two-arm, cluster-controlled design assessing the feasibility of the PCS evaluation design in five schools with seven classes receiving the PCS (henceforth intervention classes) and five classes serving as waitlist controls that received the PCS three weeks later (henceforth control classes; Figure 1).

### 2.2. Study Status

Allocation to the intervention and control groups was completed by November 19, 2021, and the PCS was implemented between 22 and 26 November 2021. Data collection was concluded by December 2021. Data cleaning and analysis is anticipated to start in May 2022.

### 2.3. Setting

All schools in Germany, without restrictions in terms of location, school type and grade, can participate in the PCS. To invite schools, we disseminated information on the content and delivery of the PCS via all state ministries of education. In addition, we used social media channels and newsletters of the Fridays for Future, Students for Future and Teachers for Future networks, the PCS newsletter and the network of schools established during previous offerings of the PCS in November 2020 and May 2021.

### 2.4. Recruitment Strategy

An overview of the recruitment strategy is provided in the CONSORT flowchart (Figure 1). While all classes of any grade including primary schools can participate in the PCS, the pilot study specifically targeted adolescents. We therefore recruited a convenience sample of classes covering grades 7 to 13 (mostly attended by adolescents aged 12 to 19 years) to participate in the pilot study. With the aim of preparing a pragmatic effectiveness study, we did not specify further inclusion or exclusion criteria for classes. In October 2021, using the newsletter of the PCS, we invited all 7500 schools in 14 federal states as well as 64 schools that had participated in previous PCS and were registered for the present PCS to participate in the pilot study. By 19 November 2021, twelve classes from five schools had consented to participate in the pilot study. 

To recruit adolescents, we invited all students in participating classes to take part in the pilot study by distributing a leaflet on the purpose and conduct of the study. All student participants and their parents provided written informed consent. To strengthen the generalisability of our findings, we did not apply any inclusion or exclusion criteria. However, students lacking German language skills that would allow them to complete a short questionnaire in German were excluded de facto.

### 2.5. Intervention

The goal of the PCS is to increase students’ knowledge about the climate crisis, empower them to become change agents and thus to create the basis for initiating and helping to shape far-reaching climate action. With the aim of bridging the gap between knowledge and action, the PCS goes beyond pure knowledge transfer and focuses more on action-oriented learning in projects, role plays and encounters.

Together with experts from science and society, the implementation team developed the PCS in 2019. Although initially targeted at university students, the PCS was first implemented in November 2020 in primary and secondary schools using tailored content and materials. The PCS is rooted in ESD with its principles of forward thinking, interdisciplinary knowledge, autonomous action and participation in social decision-making processes [29]. Moreover, the PCS is guided by the 17 United Nations Sustainable Development Goals. Prior to its first implementation in November 2020, one lesson was pretested with one class to test technical and on-site procedures at the school. No changes were made to content or delivery after the pretest. Since this time, the content and delivery of the PCS has been constantly refined based on field reports and reflection meetings of the implementation team. 

In its current form, the PCS lasts for five days, is implemented twice a year in May and November and focuses on the climate crisis and related topics such as biodiversity loss [30], climate justice (i.e., attitudes and actions supporting the just division and fair distribution of benefits and burdens of and responsibilities to tackle climate change) [31], climate communication [1], economic impact of the climate crisis [32], visions of a sustainable future [33] or climate and arts [34]. Based on prior work suggesting positive effects of tailoring strategies on intervention effectiveness [35], the PCS is tailored to local needs at two levels. At the level of classes, teachers decide autonomously which intervention components they take part in. At the level of intervention components, complementing the highly standardised live lessons delivered centrally by the implementation team, the challenges of the day, workshops and peer exchange sessions are tailored to local students’ needs. 

Intervention components developed and implemented to this point include:

**(1) Live lessons on YouTube:** Four standalone live lessons per day that can be incorporated into classroom teaching individually are the backbone of the PCS. Lessons last 45 min each and are broadcast via the PCS YouTube channel. The lessons are suitable for different grades and are delivered by teams of students with activist backgrounds and subject experts, including university teachers and researchers, from different institutions with expertise in the focus area of the respective lesson. The lessons, which emphasise the importance of critical thinking, provide basic knowledge about the climate crisis and its impact in different social and scientific fields (e.g., economics, politics). 

Students follow live broadcasts on YouTube and are encouraged to actively participate in lessons. Active participation is encouraged by several aspects. First, in addition to phases focused on building knowledge, each lesson comprises a phase for discussions and mutual exchange between students. Second, survey tools enable online interaction between experts and students. Third, worksheets accompanying each lesson invite students to become active themselves.

During the PCS, the implementation team collaborates with teachers on site. While the presenters are primarily responsible for the actual knowledge transfer, the teachers are in direct contact with students and provide technical support and non-technical assistance, including the distribution of worksheets. 

Live lessons are recorded and provided online together with worksheets and other supplementary materials, including syllabi and podcasts (https://publicclimateschool.de, accessed on 1 March 2022). This enables asynchronous participation in the PCS and makes participation of teachers outside their subject area possible.

**(2) Climate-related challenges of the day:** On each day of the PCS, classes can optionally participate in the challenge of the day, a format that encourages students to further explore specific topics and enables them to take action by initiating their own projects and activities. Activities include, inter alia, recording impacts of humans on the environment in poems, podcasts or videos, preparation of material for climate protests, writing letters to politicians at local, state or federal levels demanding comprehensive mitigation and adaptation measures or identifying further possibilities to take action on the climate crisis. The challenges aim at strengthening students’ self-efficacy and agency. They are announced directly before the live sessions on the YouTube channel and are published on the PCS website. Participating teachers and students decide autonomously whether and how to participate in the challenges. Reporting of activities to the implementation team is at the discretion of teachers.

**(3) Workshops:** Workshops are interactive and focus on specific topics such as food waste, climate justice, climate-induced migration or creative writing in light of the climate crisis. The workshops are delivered online or on site at schools by cooperation partners such as other educational institutions. The implementation team discusses the workshops with the organisers in advance but is not involved in content development or delivery.

**(4) Peer exchange sessions:** Peer exchange sessions include presentations of good practice examples and provide opportunities for participants to share their own experiences and projects with each other and to network. Peer exchange sessions are facilitated by members of the implementation team.

Teachers and school principals interested in participating in the PCS receive detailed information about the aims and procedures of the PCS during online events run by the implementation team prior to the start of the PCS. 

### 2.6. Social Identity Model of Pro-Environmental Action as Tentative Programme Theory

Previous work highlights the value of applying a programme theory a priori in the development and evaluation of complex interventions [28]. While several concepts, such as the principles of ESD, guided the development, content and delivery of the PCS, in the absence of a previously established programme theory, we used the Social Identity Model of Pro-Environmental Action (SIMPEA) [36] to guide the selection of outcomes for this pilot study (Figure 2). While there are various other theoretical models in the field that could explain climate action, including the theory of planned behaviour, the norm activation theory and the comprehensive action determination model [37,38,39], we chose the SIMPEA because, unlike the other models, it specifically intends to explain the complex interplay of collective factors that influence the appraisal of environmental crises and thus climate action, the main objective of the PCS. 

According to the model, pro-environmental behaviour is a response to the climate crisis aimed at attenuating human-induced climate change and its impacts. This response, in turn, is a function of social identity-based predictors: the more strongly people identify with a relevant pro-environmental in-group, the more efficacious they feel, and the more salient respective pro-environmental values and norms within a group are, the higher the likelihood of performing pro-environmental behaviours. Specifically, the model proposes that the interaction of these variables affects both the appraisal of environmental crises that, in turn, can trigger (collective) emotions that affect individuals’ efficacy beliefs, norms and whether and how people identify with certain groups, as well as responses.

This recursive model has recently been applied in the context of protests for climate justice [40], and it has become a useful framework for explaining social and psychological determinants of climate action (e.g., pro-environmental behaviour directed towards reducing greenhouse gas emissions) [41]. Applying this model to the PCS would therefore suggest effects on increased intentions to engage in climate action by, inter alia, (1) increasing identification with civil society groups involved in climate action, (2) affecting emotions related to the climate crisis and (3) improving individual and collective efficacy beliefs. 

### 2.7. Allocation of School Classes to Intervention or Control Group

The unit of allocation was school classes. Due to logistical constraints, allocation to the intervention and control group was performed locally by teachers. Teachers participating in the pilot study with two classes allocated the classes by tossing a coin. Teachers participating in the pilot study with one class only allocated their class to the intervention or control group without constraints.

### 2.8. Allocation Concealment and Blinding

Classes were allocated to intervention and control groups directly after recruitment ensuring allocation concealment. Due to the nature of the intervention, it is not possible to blind students, teachers, school principals or the implementation team to the intervention status of a school class, but researchers analysing the data will be blinded.

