### 2.12. Analysis

To assess participant retention, we will examine differences between the retained subsample (data provided on both assessments) and the subsample lost to follow-up regarding baseline values of sociodemographic and outcome measures using a dichotomous retention variable and logistic regression models. Proportions of students participating in the online and paper–pencil survey modes will be analysed descriptively. Problems during data collection will be abstracted from reports submitted by teachers and structured thematically to improve the implementation of the future effectiveness and process evaluation.

To uncover missingness patterns [59], missing data will be assessed across different variables. To detect potential missingness mechanisms, we will investigate associations between dichotomous variables identifying respondents with missing data and sociodemographic measures using logistic regression models. Cronbach’s alpha will be used to investigate internal consistency of scales. After computing mean scores, scale distributions as well as floor and ceiling effects will be analysed descriptively.

In a randomisation check, we will examine the balance of outcomes and sociodemographic measures in the baseline data between the intervention and control arm. The continuous primary outcome (intentions of students to reduce their ecological footprint) will be compared between the intervention and control arm with an intention-to-treat analysis using a linear mixed model containing a dichotomous intervention group variable and a random effect for school classes to account for the nested data structure [60]. Secondary outcomes will be compared between the two study arms using analogous linear mixed models.

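### The protocol claims allocation concealment and plans a randomisation check, but teachers allocated their own classes, some by free choice, so allocation was unconcealed and partly non-random

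*Protocol article*

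**What the plan says.** Section 2.7 describes the mechanism: "allocation to the intervention and control group was performed locally by teachers". It gives two rules. The first is "Teachers participating in the pilot study with two classes allocated the classes by tossing a coin". The second is "Teachers participating in the pilot study with one class only allocated their class to the intervention or control group without constraints".

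Section 2.8 then says: "Classes were allocated to intervention and control groups directly after recruitment ensuring allocation concealment".

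Section 2.12 plans the baseline comparison under a randomised-trial label: "In a randomisation check, we will examine the balance of outcomes and sociodemographic measures in the baseline data between the intervention and control arm". The same section compares the arms by intention to treat in a linear mixed model. The terms it names are the group variable and a random class effect, and it does not distinguish coin-tossed from chosen classes.

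On numbers and dates, the Abstract reports: "Seven and five classes were allocated to the intervention and waitlist control arms, respectively". Section 2.2 reports: "Allocation to the intervention and control groups was completed by November 19, 2021".

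The Abstract and section 2.1 call the design cluster-controlled. The Limitations say that decentral allocation by teachers may disturb baseline balance and so influence parameter estimates. They reserve randomisation by a blinded statistician for the later effectiveness study.

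**The concern.** Allocation is concealed when the person who enrols or assigns a unit can neither foresee nor steer its arm. Here the teacher of the class was the allocator. A one-class teacher selected the arm, so nothing was left to conceal. A two-class teacher tossed the coin, and the article describes no independent control of the toss. Allocating soon after recruitment does not supply concealment when the allocator is an interested party.

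The label in section 2.12 compounds this. A balance check cannot verify a randomisation that part of the sample never had. With 12 classes, apparent balance on measured variables says little about unmeasured ones such as the motivation of a teacher who chose the intervention.

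At stake is how the arm contrast is read. It pools classes placed by chance with classes placed by choice, and the secondary objective is to supply parameter estimates for sizing the main trial.

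**Working it through.** **1. The sections side by side.**
- Section 2.7: the teacher assigns, by own coin toss (two classes) or by choice (one class).
- Section 2.8: concealment is said to follow from the timing of allocation. No mechanism is named that keeps the assignment from the teacher.
- Section 2.12: a randomisation check across the whole arm comparison.
- Limitations: decentral allocation is disclosed; free choice of arm is not mentioned, and the concealment statement stands.

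Sections 2.7 and 2.8 cannot both be right.

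**2. How many classes were placed by choice.** The article does not say, so only a range can be given.

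Inputs: 12 classes, 7 intervention and 5 control (Abstract, section 2.1); the two rules in section 2.7.

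Assumption A: every teacher brought one or two classes. With k two-class teachers, the number of classes placed by choice is s = 12 − 2k, which is always even. Section 2.7 reports both kinds of teacher as having allocated. At least one two-class teacher (k ≥ 1) gives s ≤ 10. At least one one-class teacher gives s ≥ 1, and because s is even, s ≥ 2.

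Assumption B: each toss sent one of the teacher's classes to each arm. Pairs then contribute k to each arm, and choice supplies 7 − k intervention and 5 − k control classes:

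| k | chosen, intervention | chosen, control | chosen, of 12 |
|---|---|---|---|
| 5 | 2 | 0 | 2 (17%) |
| 4 | 3 | 1 | 4 (33%) |
| 3 | 4 | 2 | 6 (50%) |
| 2 | 5 | 3 | 8 (67%) |
| 1 | 6 | 4 | 10 (83%) |

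In every row (7 − k) − (5 − k) = 2: the intervention arm holds two more chosen classes than control. Under B, tosses alone would give equal arms, so they cannot produce 7:5.

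**3. Timing.** Section 2.2 has allocation complete by 19 November 2021. Section 2.4 has the twelve classes consenting by the same date. Section 2.10 places the baseline survey one week before the programme, which ran 22 to 26 November. These dates do not fix the order of allocation, student consent and baseline within a class.

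**The case against.** The best defence is that the article is largely open about this. It calls the pilot cluster-controlled, states both allocation rules plainly, lists teacher allocation as its first limitation, and leaves randomisation to the later study. The primary objectives are recruitment and retention, data collection and data quality, and the Limitations rightly say that the objectives other than parameter estimation do not depend on unbiased effect estimates. Intention to treat means analysed as allocated, which is legitimate in a controlled design. Comparing baseline characteristics is also a sensible response to the disclosed limitation; only its name is wrong. All of this stands and limits the consequence. It does not rescue the concealment sentence, which the disclosure makes harder to reconcile with the rest of the article.

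Some stronger readings are tempting but unsupported:
- **That students joined knowing their arm.** Section 2.4 uses recruitment for both classes and students, so allocation may have followed student consent. The text neither shows nor excludes prior knowledge of the arm.
- **That the bias can be sized.** The document gives no baseline shift for chosen classes, and chosen control classes may be selected too. Any figure in SD units would only restate an assumption.
- **That all 12 classes were self-allocated.** Section 2.7 reports that two-class teachers did toss coins.
- **That the arm difference is meant to set the main trial's effect size.** The Discussion speaks of initial parameter estimates combined with external evidence, including published intra-class correlations, and does not say this.

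**Conclusion.** The concealment statement in section 2.8 is wrong as written, and randomisation check is the wrong name for the comparison in section 2.12. Allocation was unconcealed and partly by teacher choice. Between 2 and 10 of the 12 classes were placed by choice, assuming one or two classes per teacher and taking section 2.7 at its word that both kinds of teacher took part. The excess of two chosen classes in the intervention arm further assumes that each toss split a pair. Non-randomised describes the 7 versus 5 comparison as a whole; the coin-tossed pairs were allocated by chance if the tosses were honoured.

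The consequence falls on the arm contrast and on any use of it under the secondary objective. This should be corrected, but it is not a fault that undermines the pilot.

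**What to change.** 1. In section 2.8, delete the claim that concealment was ensured. State that allocation was unconcealed and partly by teacher choice, and add free choice of arm to the Limitations.
2. In section 2.12, rename the check a baseline comparability assessment and show it by arm and by allocation mode (coin toss or teacher choice).
3. Report how many classes were coin-tossed and how many were chosen.
4. Show the estimate for the coin-tossed pairs beside the pooled estimate, and label the pooled estimate non-randomised.
5. Report consenting over eligible students by arm, because the text does not rule out that the arm was known before student consent. The teacher protocol sheets in section 2.10 already ask for the number eligible.
6. State that the pooled arm difference will not be used as the main trial's target effect.

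The cost is a text correction, one stratified table and one subset estimate. Section 2.2 anticipates data cleaning and analysis from May 2022, so all of this can be settled before analysis starts. The downside is that the coin-tossed subset has at most five pairs under the counts above, so its interval will be wide and the subset estimate is descriptive only.
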